## Abstract

**Background:**

The number of people with dementia is rising rapidly as a consequence of the greying of the world population. There is an urgent need to develop cost effective approaches that meet the needs of people with dementia and their family caregivers. Depression, feelings of burden and caregiver stress are common and serious health problems in these family caregivers. Different kinds of interventions are developed to prevent or reduce the negative psychological consequences of caregiving. The use of internet interventions is still very limited, although they may be a cost effective way to support family caregivers in an earlier stage and diminish their psychological distress in the short and longer run.

**Methods/design:**

A pragmatic randomized controlled trial is designed to evaluate the effectiveness and cost-effectiveness of ‘Mastery over Dementia’, an internet intervention for caregivers of people with dementia. The intervention aims at prevention and decrease of psychological distress, in particular depressive symptoms. The experimental condition consists of an internet course with 8 sessions and a booster session over a maximum period of 6 months guided by a psychologist. Caregivers in the comparison condition receive a minimal intervention. In addition to a pre and post measurement, an intermediate measurement will be conducted. In addition, there will be two follow-up measurements 3 and 6 months after post-treatment in the experimental group only. To study the effectiveness of the intervention, depressive symptoms are used as the primary outcome, whereas symptoms of anxiety, role overload and caregiver perceived stress are used as secondary outcomes. To study which caregivers profit most of the internet intervention, several variables that may modify the impact of the intervention are taken into account. Regarding the cost-effectiveness, an economic evaluation will be conducted from a societal perspective.

**Discussion:**

This study will provide evidence about the effectiveness and cost-effectiveness of an internet intervention for caregivers. If both can be shown, this might set the stage for the development of a range of internet interventions in the field of caregiving for people with dementia. This is even more important because future generations of caregivers will be more familiar with the use of internet.

**Trial registration:**

NTR-2051/RCT-DDB

## Background

In a recent report on the global economic impact of dementia
[1], costs of dementia are estimated to be slightly over US$600 billion pro year worldwide. Costs include direct medical costs, direct costs of social care and costs attributed to informal care. As a consequence of the growing number of dementia patients, costs will rise in the future. Alzheimer’s Disease International has tentatively estimated an 85% increase in costs in 2030, based only on predicted increases in the number of people with dementia. As a consequence, there is a strong plea to invest in research and the development of cost effective approaches that meet the needs of people with dementia and their caregivers across the course of the illness.

Most people with dementia live at home and are cared for by their spouses, children or other family members. These caregivers play a crucial role in the quality of life and quality of care of their family members. Caring for a spouse with dementia can be a highly stressful experience associated with negative caregiver outcomes such as high rates of burden, psychological morbidity, depression and poorer immune function
[2,3]. Different kinds of interventions have been developed for caregivers of people with dementia
[4-7]. The majority of these interventions consists of psycho-educational programs providing information on dementia and the consequences for daily living, how to cope with related problems, which services are available and how to get help.

Research has shown that particular types of interventions are effective. One of the main characteristics of effective interventions is a psychological rather than purely educational approach
[8]. Psychological treatment is aimed at improving caregivers’ abilities to cope with problem behavior or stressful situations or to enhance communication skills and asking support from others
[9]. A recent review shows that psychological therapies and psychosocial interventions may be a potentially cost effective approach to improve outcomes and quality of life in both people with dementia and their family caregivers
[10].

Several meta-analysis of randomized controlled trials on the effectiveness of internet interventions for depression or anxiety focusing on other target groups such as younger adults with depression, show that interventions are effective
[11-14], even more if therapist support is part of the intervention
[15]. There is also growing evidence that internet-based interventions are cost effective
[16]. Family caregivers may favor internet interventions instead of meeting in a group or meeting with a professional face-to-face, due to lack of time or preferences concerning privacy. Caregivers may also be unwilling to visit a mental health care institute for themselves because in their view they are not the ones who need help. Given the growing internet sophistication of middle aged and older adults, it is expected that the number of potential users of internet interventions will grow substantially.

Until recently internet-based interventions were not developed for family caregivers of people with dementia. In November 2008, the innovative eMental Health intervention for family caregivers of people with dementia, called ‘Mastery over Dementia’, was launched in the Netherlands (for an English demo:
http://www.masteryoverdementia.com). In this paper the design of the RCT to evaluate the effectiveness and cost-effectiveness of ‘Mastery over Dementia’ for caregivers of people with dementia will be described. The specific research questions are:

1. Is ‘Mastery over Dementia’ superior compared to ‘care as usual’ in terms of a clinically significant reduction in depressive symptoms, symptoms of anxiety, role overload and caregiver perceived stress?

2. Are effects maintained up to six months after ending the internet intervention?

3. Which caregivers respond best to the intervention compared to others?

4. Is the internet intervention cost effective from a societal perspective compared to the comparison group?

## Methods and design

To evaluate the effectiveness of ‘Mastery over Dementia’, we carry out a pragmatic randomized control trial (RCT). In the RCT there are two parallel groups. The experimental condition in which caregivers take part in the intervention (Mastery over Dementia) will be compared with a comparison condition in which caregivers receive a ‘minimal intervention’. The study protocol, information brochure and informed consent procedure were approved by the Medical Ethics Committee (METIGG, CCMO: NL27434.097.09).

### Recruitment

Participants are recruited in several ways: the website itself, the monthly digital newsletter of the Alzheimer’s Society in the Netherlands, leaflets at meetings of Alzheimer Cafes and information letters to memory clinics and other relevant care institutions. Participants are invited to fill in a first short questionnaire on the website. This questionnaire serves as a screening tool on the basis of which can be decided if participants are suitable for treatment. Caregivers will be included with a score > 4 on the Center for Epidemiological Studies-Depression scale, or a score > 3 on the HADS-A, or a minimum score of 6 on a one item burden scale ranging from 0-10. Caregivers with high scores on the CES-D and the HADS-A or having suicidal thoughts, were first contacted by an elderly care physician.

### Randomization

Randomization into two groups (experimental group and comparison group) takes place after assessment. Before randomization participants are stratified on the basis of two factors (sex: male/female and relationship: spouse/other). As a method for randomization block randomization with variable sizes is used. The allocation schedule is made with a computerized random number generator by an independent researcher and is unknown to the investigators of this study.

### Interventions

#### Experimental condition

The intervention ‘Mastery over Dementia’ was developed by the Netherlands Institute of Mental Health and Addiction in collaboration with a specialized Dutch health care provider (Geriant) and the Alzheimer’s Society in the Netherlands (Alzheimer Nederland)
[17]. The program offered is a combination of evidence-based support strategies: psycho-education, cognitive behavioral therapy, problem solving therapy and assertiveness training. Relaxation is also incorporated. During the intervention, caregivers are supported on-line by a psychologist (coach) who gives feedback on the exercises sent by the caregivers. The coach has been trained in cognitive behavioral therapy.

‘Mastery over Dementia’ consists of eight lessons and a booster session (follow-up). Each lesson consists of information, practice rehearsal and some homework. Themes covered in the course are, for example:

– coping with behavioral problems

– arranging help from others

– non-helping en helping thoughts

– communicating problems

#### Comparison group

Caregivers in the comparison group receive a minimal intervention. There is no contact with a coach. The intervention consists of eBulletins with practical information about caring for someone with dementia. The bulletins are sent by mail according to a fixed schedule. Topics of the bulletin do not overlap with the content of ‘Mastery over Dementia’. Topics covered in the bulletins include:

– Driving and dementia

– Holiday breaks

– Medication and dementia

– Activities throughout the day

– Grieving and dementia

– Safety measures in the home

### Measures and measurement

There are 3 measurements in both groups. The first measurement is at baseline (pretest). The second measurement takes place halfway during the intervention course (after the fourth lesson) or after the receipt of the fourth bulletin (comparison group). This is approximately at 3 months after baseline. The third measurement (post-test) is conducted directly after the intervention (about 6 months after baseline). Additional measurements for the experimental group are at three months (9 months after baseline) and six months after completion (12 months after baseline). All measurements are self-report measures and are administered through the Internet. In both conditions automated emails are sent to participants asking them to fill in the questionnaires. This is repeated when participants do not respond within a week, and for a second time after two weeks. If participants do not answer a research assistant contacts them by phone.

#### Outcome measures in the RCT

For an overview of the instruments see Table
1.

**Table 1 T1:** Overview of instruments (measures)

	**Pre-test**			**Post-tests**		
	**Intake**	**T = 1**	**T = 2**	**T = 3**	**T = 4**	**T = 5**
Outcome measures in the RCT						
-* Depressive symptoms: CES-D*	X		X	X	X	X
- *Anxiety symptoms: HADS-A*	X		X	X	X	X
- *Role overload: SPPIC*		X	X	X	X	X
- *Caregiver perceived stress: RMBPC*		X		X	X	X
Confounders/Modifying variables						
- *Perceived control: Mastery Scale*		X		X	X	X
- *Sense of competence: SSCQ*		X		X	X	X
- *Behavioral problems: RMBPC*		X		X	X	X
- *Demographic variables*	X					
- *Diagnosis/Duration of symptoms*	X					
- *Functional status of person with dementia: IQCODE*	X					
Outcome measures in the CEA						
- *Quality of life: EQ-5D+C*		X		X	X	X
- *Health care utilization: TIC-P*		X		X	X	X
- *Time spent on caregiving*	X			X	X	X

*CES-D* Centre for Epidemiological Studies Depression scale.

*EQ-5D+C* EuroQol 5 Dimensions plus Cognition.

*HADS-A* Hospital Anxiety and Depression Scale, Anxiety subscale.

*IQCODE* Informant Questionnaire on Cognitive Decline in the Elderly.

*RMBPC* Revised Memory and Behavioral Problem Checklist.

*SPPIC* Self Perceived Pressure from Informal Care scale.

*SSCQ* Short Sense of Competence Questionnaire.

*TIC-P* iMTA Questionnaires on Costs Associated with Psychiatric Illness.

##### Primary outcome measure: depressive symptoms

Depressive symptoms are measured with the Centre for Epidemiological Studies Depression scale (CES-D). The CES-D is a widely used self-report measure for the screening of depressive symptoms, and has also been used in research on caregiving. The Dutch version of the CES-D
[18] is used in this study. It consists of 20 items for which subjects rate the frequency of symptoms during the past week. Scores range from 0 (rarely or none of the time present [less than 1 day]) to 3 (most or all of the time present [5-7 days]). The total score range is 0–60. Items represent major components of depressive symptomatology such as depressed mood, feelings of guilt and worthlessness, feelings of helplessness and hopelessness, psychomotor retardation, loss of appetite, and sleep disturbance. A shortened version of the CES-D on internet (not used in this study) was found to be reliable in an adult population
[19].

##### Secondary outcome measure: anxiety symptoms

The 7-item anxiety subscale (Dutch version) of the Hospital Anxiety and Depression Scale
[20] is used to measure the severity of anxiety symptoms. The Hospital Anxiety and Depression Scale (HADS) is an extensively used, brief self-report screening scale to investigate the prevalence of depression and anxiety symptoms. The anxiety subscale consists of 7 items rated on a scale ranging from 0 (not at all) to 3 (a great deal of the time). Total score ranges from 0 to 21 with higher scores indicating more anxiety. The Dutch version of the HADS shows good reliability in normal and clinical Dutch samples
[21].

##### Secondary outcome measure: role overload

Feelings of role overload are measured by means of the Self Perceived Pressure from Informal Care scale (SPPIC)
[22]. The SPPIC consists of 9 items, answers vary from 0 (totally disagree) to 4 (totally agree). The SPPIC is a one-dimensional hierarchical scale; higher scores mean more perceived pressure. The items are summed on the basis of dichotomized scores (cut off: totally disagree and disagree = 0; other answers = 1). Total scores range from 0 – 9. The original study
[23] shows that reliability is good and that perceived pressure did not differ for male and female caregivers, and for spouse and non-spouse caregivers.

##### Secondary outcome measure: caregiver perceived stress

The Dutch version
[24] of the Revised Memory and Behavioral Problem Checklist (RMBPC)
[25] is used for measuring caregiver perceived stress. The questionnaire lists 24 items reflecting a variety of problems caregivers can encounter. Respondents have to rate the frequency of the occurrence of the specific behavior from 0 (never) to 4 (always). Each item rated with a score of 1 (seldom) of higher, is presented again raising the question how much people are stressed by the occurrence of the behavior (4-point scale from not at all stressed to very much stressed). The Caregiver Reaction Score is calculated as a mean score for all items together and additionally can be divided in separate reaction scores on depressive behavior (9 items), disruptive behavior (8 items) and memory-related behavioral problems (7 items). Overall scale reliability is good
[24].

#### Additional measures in the RCT

##### Perceived control

Perceived control of events and ongoing situations will be assessed using a translated and abbreviated 5-item version of the Pearlin Mastery Scale. The original scale has 7 items regarding how much an individual perceives having control over things in his or her life. The scores per item vary from 0 (totally disagree) to 4 (totally agree). The Mastery Scale
[26] has good psychometric properties. Compared to the original questionnaire, in the abbreviated version two items phrased in a positive way (‘I can do just about anything I really set my mind to’ and ‘What happens to me in the future mostly depends on me’) are left out. This abbreviated version shows good reliability
[27]. Items are summed for a total mastery score (ranges from 0 to 20) with lower scores indicating greater perceived control.

##### Sense of competence

Caregiver’s sense of competence will be assessed by means of the Short Sense of Competence Questionnaire (SSCQ)
[28]. The SSCQ consists of 7 items. Responses are rated on a 5-point scale with possible answers, ranging from totally agree (0) to totally disagree (4). The questionnaire has three dimensions: consequences for personal life of the caregiver (2 items), satisfaction with role of the caregiver themselves (2 items) and satisfaction with role of the person with dementia (3 items). The items are summed on the basis of dichotomized scores (cut off: totally disagree and disagree = 1; other answers = 0). Total score range from 0 – 7.

##### Frequency of reported behavioral problems

The 24 items of the Revised Memory and Behavioral Problem Checklist (RMBPC)
[25] are used to make an inventory of the number of problems family caregivers encounter. Respondents have to rate from 0 to 4 the frequency of the occurrence of the specific behavior (0 = never; 1 = seldom; 2 = regularly; 3 = often; 4 = always). The total number of behaviors problems (0 – 24) will be calculated as well as the total mean score (Behavior Frequency Score). The Behavior Frequency can be subdivided into scores on Depression (9 items), Disruptive behavior (8 items) and Memory-related problems (7 items).

Other variables that may act as confounders or modifying variables will be measured. This concerns the following demographic characteristics of caregivers: sex, age, relationship (spouse, child or other), level of education and living arrangement (living together with care recipient). Relevant patients characteristics are: sex, age, duration of symptoms (as perceived by caregiver), functional status (assessed by means of a Dutch translation of a short version of the IQCODE
[29]) and living condition (independently or within care facility).

#### Outcome measures in the economic evaluation

For an overview of the instruments see Table
1.

##### Quality of life

Quality of life will be measured using the 6-item self report instrument EQ-5D+C
[30]. The EQ-5D+C is an extended version of the EuroQol
[31] which measures health related quality of life and consists of five dimensions (mobility, self-care, main activity, pain and mood). The EQ-5D+C adds ‘cognition’ as a sixth dimension. Each dimension is rated as causing 'no problems', 'some problems' or 'extreme problems'. The EuroQol valuations appear to have good test-retest reliability
[32]. QALYs will be calculated using the Dutch EuroQol tariff to estimate utilities
[33].

##### Health care utilization

An adapted version of the iMTA Questionnaires on Costs Associated with Psychiatric Illness (TIC-P) will be used to measure health care utilization and productivity losses
[34]. In this study both the direct costs related to the person with dementia with dementia and the direct costs related to the situation of the family caregivers themselves are measured. Direct costs will include the number of consultations with health care providers (e.g. general practitioner, physical therapist, psychologist, medical specialist, etcetera), medication, and admissions to hospitals and other institutions. Indirect costs are defined as the productivity lost due to absenteeism from paid and unpaid work and reduced efficiency at work (presenteeism).

##### Time spent on caregiving

This is measured by four questions tapping several main areas of caregiving (household tasks, personal hygiene, transportation outside, finances and administration). Caregivers are asked to estimate to total numbers of hours in the past week. In addition to this we also collect information on the availability of other informal caregivers and volunteers and the amount of time these others spent on caregiving for the person with dementia. Total amount of time the family caregiver spends on providing care and also the total amount of time spent by other informal caregivers or volunteers is calculated.

### Sample size

Symptoms of depression are the primary outcome measures and are used as starting point for the power calculations. A standardized effect size (Cohen's *d*) of 0.50 is considered a relevant treatment effect. Assuming an alpha of 0.05 and a statistical power (1-Beta) of 0.80 in a two-tailed test, we need 63 respondents in each of the conditions. Overall, we need 126 respondents to complete the study in total. Because we expect a minimum of 25 percent of caregivers to drop out during the data collection, we will recruit at least 175 caregivers. The numbers are calculated in Stata 7.0 (StataCorp 2001).

### Statistical analysis

All analyses in the RCT-study will be conducted according to the intention to treat principle. Missing data on follow-up measurements will be imputed using regression imputation. To examine differences between the outcomes for experimental and comparison group, paired t-tests will be conducted and estimates of effect sizes will be calculated. By using multiple regression analyses, we can correct for possible confounders. With a ‘generalized estimated equations’ (GEE) analysis the research question regarding the maintenance of the effectiveness of the intervention will be answered. In addition, profiles of caregivers who respond best to the intervention will be described by means of a multiple regression analysis which also contains modifying variables (modifier analysis). All analyses will be conducted using SPSS for Windows, version 19.

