#### Economic analyses

This economic evaluation will involve both a cost-effectiveness analysis (CEA) and a cost-utility analysis (CUA). Incremental cost-effectiveness ratios will be calculated by dividing the difference in total costs between conditions by the difference in average effect size. Because we calculate costs over a period of six months, correction for inflation is not necessary. Missing data on follow-up measurements will be imputed using multiple imputation. Bias-corrected and accelerated bootstrapping with 5000 replications will be used to calculate 95% confidence intervals around the mean difference in total costs between the treatment groups. Bootstrapping will also be used to estimate the uncertainty surrounding the ICERs which will be graphically presented on cost-effectiveness planes. Cost-effectiveness acceptability curves and net monetary benefits will also be calculated. Cost-effectiveness acceptability curves show the probability that collaborative care is cost effective in comparison with usual care for a range of different ceiling ratios thereby showing decision uncertainty. Sensitivity analyses will be carried out to ascertain the robustness of the findings under different scenarios, e.g. under varying values of key-variables.

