## Discussion

This study assesses the effectiveness and cost-effectiveness of an internet intervention for family caregivers of people with dementia. In the context of the fast growing number of people with dementia in years to come, there is an urgent need to develop cost-effective approaches that meet the needs of people with dementia and their family caregivers across the course of the illness. Some family caregiver may apply for help in the beginning of the course of the illness, others may use the intervention in a later stage. The potential effect of the internet intervention may act immediately or help people to keep on caring and prevent them from developing (more) health problems.

The RCT-study is conducted in the practical setting of a health provider who is specialized in dementia care and offers case management and a variety of support strategies for persons with dementia and family caregivers. Because internet delivered intervention is highly structured and leaves little room for the therapist to adapt it, in practice the structure remains intact without major adaptation
[35]. Important advantage of such a pragmatic study is that results of the study have a high level of generalizibility.

As is the case with internet therapy (or research studies in this domain) in general
[36], we expect participants to be more highly educated, with a high proportion of them having a university degree. It is also rather common that clients drop out of (research into) internet therapy. In a recent review on dropout from internet-based treatment for psychological disorders an average rate of 31% was found
[37]. Evidence on any specific variables that may make an individual more likely to drop out is currently limited
[37]. In this study we expect some family caregivers to drop out for specific disease related reasons like admission to an nursing home or death of the person with dementia. All together this may have a negative effect on the generalizability.

Primary outcome measure in the RCT is severity of depressive symptoms of the family caregiver. Anxiety symptoms, feelings of burden and caregiver stress are secondary outcomes. In a review article about consensus on outcome measures for psychosocial intervention research in dementia care, some recommendations are made for use of specific measures

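### Regression imputation of missing RCT outcomes, read as single imputation, gives either standard errors that are too small or an effect biased toward zero, depending on whether arm is in the imputation model

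*Protocol article*

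**What the plan says.** All places are in the protocol article.

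- **Statistical analysis, analysis set:** "All analyses in the RCT-study will be conducted according to the intention to treat principle". Participants without a follow-up score therefore enter the tests.
- **Statistical analysis, missing data:** "Missing data on follow-up measurements will be imputed using regression imputation". No repeated draws, pooling or variance correction is mentioned. T-tests (called paired), multiple regression, GEE and a modifier analysis follow.
- **Economic analyses:** "Missing data on follow-up measurements will be imputed using multiple imputation".
- **Sample size:** "we expect a minimum of 25 percent of caregivers to drop out during the data collection", with a recruitment target of at least 175.
- **Discussion:** for drop-out from internet-based treatment in a cited review, "an average rate of 31% was found".
- **Table 1:** CES-D, HADS-A and SPPIC are collected at T=2 (about 3 months) and T=3 (post-test, about 6 months). RMBPC is not collected at T=2.

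**The concern.** The two missing-data sentences differ only in the method named, so the authors evidently distinguish the methods, and regression imputation reads as one predicted value per missing score. Such values carry no uncertainty of their own, yet they count as full observations.

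What follows depends on the imputation model:

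- **Arm included.** The imputed scores repeat the arm difference estimated from the observed cases. The estimate is unbiased under random loss, but its reported standard error is too small and the nominal 0.05 level does not hold.
- **Arm omitted.** The imputed scores carry no arm difference, and the effect is diluted.

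At stake is the primary CES-D comparison and, as the sentence is worded, every imputed follow-up outcome in the effectiveness analyses. The article states no missing-data sensitivity analysis for these outcomes; the one it mentions belongs to the economic evaluation.

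**Working it through.** **1. The plan's own figure.** The Sample size section states "A standardized effect size (Cohen's *d*) of 0.50 is considered a relevant treatment effect" and "Assuming an alpha of 0.05 and a statistical power (1-Beta) of 0.80 in a two-tailed test, we need 63 respondents in each of the conditions". By the normal approximation, n = 2(1.960 + 0.842)² / 0.50² = 2 × 7.85 / 0.25 = 62.8, so 63 per arm and 126 in total. This reproduces. Allowing for 25% loss, 126 / 0.75 = 168; the target of 175 covers 28% loss (126 / 175 = 0.72).

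**2. How many scores would be imputed.** If the drop-out rates applied at post-test: 175 × 0.25 ≈ 44, and 175 × 0.31 ≈ 54.

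**3. Inputs not in the article (assumptions).** Baseline-outcome correlation ρ of 0.3, 0.5 and 0.7; scores missing completely at random with fraction p; equal arms; deterministic imputation from the baseline score; a between-arm test.

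**4. Arm in the imputation model.** With outcome variance 1 and n per arm:

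- Unadjusted t-test: the true variance of an arm mean is about [ρ² + (1−ρ²)/(1−p)] / n. The variance reported from the completed data is about [ρ² + (1−ρ²)(1−p)] / n. R, the ratio of reported to true standard error, is the square root of reported over true variance.
- Baseline-adjusted regression: R ≈ 1 − p, whatever ρ is.
- Two-sided type I error ≈ 2[1 − Φ(1.96 R)].

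Example, p = 0.25 and ρ = 0.5, t-test: R = √[(0.25 + 0.75 × 0.75) / (0.25 + 0.75/0.75)] = √(0.8125/1.25) = 0.806, and type I error = 2[1 − Φ(1.580)] = 11.4%. Adjusted regression: R = 0.75, and type I error = 2[1 − Φ(1.47)] = 14.2%.

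The formulas were checked by simulation (175 randomised, no true effect, 20,000 trials per setting):

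| p | ρ | t-test, formula | t-test, simulated | Adjusted, formula | Adjusted, simulated |
|---|---|---|---|---|---|
| 0.10 | 0.3 | 7.5% | 7.6% | 7.8% | 7.7% |
| 0.10 | 0.5 | 7.0% | 7.0% | 7.8% | 7.6% |
| 0.10 | 0.7 | 6.3% | 6.1% | 7.8% | 7.6% |
| 0.15 | 0.3 | 9.1% | 8.9% | 9.6% | 9.5% |
| 0.15 | 0.5 | 8.3% | 8.3% | 9.6% | 9.7% |
| 0.15 | 0.7 | 7.1% | 7.3% | 9.6% | 9.7% |
| 0.25 | 0.3 | 13.1% | 13.4% | 14.2% | 14.4% |
| 0.25 | 0.5 | 11.4% | 11.5% | 14.2% | 14.8% |
| 0.25 | 0.7 | 9.1% | 9.2% | 14.2% | 14.6% |
| 0.31 | 0.3 | 16.2% | 16.7% | 17.6% | 18.2% |
| 0.31 | 0.5 | 13.8% | 14.1% | 17.6% | 18.2% |
| 0.31 | 0.7 | 10.5% | 10.8% | 17.6% | 18.1% |

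At 25–31% missing the simulated R runs from 0.68 to 0.86.

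Variants, from smaller simulations:

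- Adding one random residual to each imputed score still gives about 8–14% at 25–31% missing.
- Using the T=2 score as a further predictor (assumed T=2 to T=3 correlation 0.7, T=2 observed for everyone) gives about 9–11% at 25% and 10–12% at 31%.

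**5. Arm left out of the imputation model.** The expected difference is about (1 − p)d: 0.75 × 0.50 = 0.375 and 0.69 × 0.50 = 0.345. Simulated means are 0.37 and 0.34–0.35. Type I error stays near 5%, but 95% intervals cover the true d of 0.50 in only 59–86% of trials.

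**6. Under the alternatives.** In the same settings at 25–31% missing, multiple imputation (20 draws, Rubin's rules, baseline-adjusted) gives type I error of 4.8–5.2%. Analysing observed cases only gives 4.4–5.2%.

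**The case against.** Several objections have force.

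- **The word single is not in the text.** It is inferred. The contrast with the economic section makes the inference strong, and since the article names the method, this is not a detail left to an unseen analysis plan. The content of the imputation model is such a detail, so the result must be stated for both cases. A reader might infer that the standard errors are bound to be too small. The article does not support that: with arm omitted they are about right under the null, and the harm is dilution of the effect.
- **The missing fraction at post-test is not given.** The 25% refers to the whole data collection, which runs to 12 months in the experimental arm, whereas the between-arm comparison ends at about 6 months. The 31% is drop-out from treatment in other studies. The plan also has two e-mail reminders and a phone call. A reader might take 25–31% as the expected loss at T=3; the article does not say so. At 10–15% missing the inflation is smaller but still present.
- **The test simulated is not the one named.** The article says paired t-tests. The figures here apply to a between-arm comparison, which the superiority question requires.
- **Two methods in one trial.** A reader might count the difference between the clinical and economic sections as an error in itself. It is not: scores and cost data may reasonably be handled differently. It matters only if the same clinical score is also the effect in the cost-effectiveness ratio, which the article does not specify.

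These points limit the size and certainty of the figures. None of them makes the named method sound.

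**Conclusion.** The concern stands in conditional form, and the method is wrong as written. For a between-arm comparison, with random loss and ρ assumed at 0.3–0.7:

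- **Arm in the imputation model:** two-sided type I error is about 9–18% at 25–31% missing, and roughly 7–10% at 10–15% missing (6% in the most favourable cell).
- **Arm omitted:** type I error is near 5%, but a true d of 0.50 is estimated as about 0.37 at 25% missing and 0.34 at 31%.

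The direction is secure in each case. The exact size rests on the assumed correlation, the missing fraction at T=3, the loss mechanism and the predictors used, none of which the article fixes. In the random-loss settings tried, analysing the observed cases alone held the 5% level, which single imputation with arm did not.

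**What to change.** In the Statistical analysis section, replace regression imputation with multiple imputation pooled by Rubin's rules. Put these in the imputation model:

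- arm;
- the baseline score;
- the stratification factors (sex and relationship);
- the T=2 score where Table 1 shows it is collected, that is for CES-D, HADS-A and SPPIC but not for RMBPC.

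Alternatively, use a likelihood-based mixed model on all observed scores for the outcomes measured at both T=2 and T=3, and a baseline-adjusted model for RMBPC, with no imputation.

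The clinical and economic analyses need not share one missing-data method. If the same clinical score also serves as the effect in the cost-effectiveness ratio, the two effect estimates should be consistent.

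The cost is a change of wording: no new data or participants are needed, and the trial already plans multiple imputation for its economic part. The downside is wider confidence intervals than single imputation would report, which is the honest width.
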